### Interventions

Low-dose IV infusion of ATP (20–40 mcg/kg/min) has been shown to be safe in multiple clinical trials [29, 30]. Therefore, IV administration of 100 mg ATP (40 mcg/kg/min) twice daily was chosen in this study. PCr has been used in muscle hypotonotrophy, acute and chronic ischemic heart disease, heart failure conditions, and ischemic stroke. Clinically, no serious side effects have been reported for the IV administration of 1–2 g of PCr daily for the treatment of the above-mentioned diseases [31]. Besides, clinical studies have reported the safety of 3–5 g/day of orally administered creatine for MDD [32–34]. Our animal studies found that intraperitoneal injection of 125 mg/kg PCr in depressed rats producing the best efficacy; thus, IV administration of PCr at 1 g (125 mg/kg × 0.08 × 60 kg) twice daily was chosen in this study [35].

Enrolled patients will be hospitalized for the initial 14 days. All patients will receive one fluoxetine tablet (Eli lilly and company, State Food and Drug Administration (SFDA) approval No. J20160029, 20 mg per day, at 08:00). For the ATP and PCr groups, adenosine disodium triphosphate (Guangzhou Baiyunshan Tianxin pharmaceutical corporation, SFDA approval No. H44023293, 100 mg, 10 ml) or sodium phosphocreatine (Harbin Laiboten pharmaceutical corporation, SFDA approval No. H20054352, 1 g in 10 ml of 0.9% saline) diluted in 100 ml of 0.9% saline will be administered intravenously twice daily (at 08:00 and 16:00). IV administration should be completed within 40 min (40 drops per min) of time of dilution. In the control group, patients will receive 110 ml of 0.9% saline in equivalent procedures. In total, we will provide continuous orally administered fluoxetine therapy for 6 weeks, and intravenously administered medical treatment will proceed during hospitalization.

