## Discussion

Multiple studies have revealed altered energy metabolism in brain regions. With the utilization of in-vivo phosphorous magnetic resonance spectroscopy, nucleoside triphosphate (NTP), which mainly derives from ATP, has shown to be decreased in depressed subjects [45]. Meanwhile, in MDD patients treated with either SSRI sertraline, or creatine, or thyroid hormones, which have been shown to increase brain bio-energetic metabolism, NTP levels are significantly increased in treatment responders compared with non-responders [26, 46, 47]. Compared with conventional ADs, novel compounds with fast-acting AD effects will minimize the time lag to obtain treatment results, enhance patients’ adherence, reduce the suicide rate and aid psychosocial recovery.

Our preclinical studies showed that ATP, as well as PCr, displayed rapid AD effects in animal models of depression. To our knowledge, our study is the first clinical attempt to add ATP/PCr intravenously with the orally administered fluoxetine to patients with moderate to severe MDD.

PCr, after being diluted in 0.9% saline 100 ml, should be infuse intravenously within the next 40 min. As this is a double-blinded experiment, both ATP and placebo group should be administered in less than 40 min. However, if the infusion rate of ATP is too fast, some patients might experience palpitations. We assume that the nocebo effects might influence the efficacy results in ATP group.

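### A fixed 100 mg ATP dose over 40 min is 40 mcg/kg/min only at 62.5 kg; every lighter patient is above the range the protocol cites as safe

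*Protocol article*

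**What the plan says.** The Interventions section opens its case for the ATP dose with a safety statement: "Low-dose IV infusion of ATP (20–40 mcg/kg/min) has been shown to be safe in multiple clinical trials". It then concludes that "IV administration of 100 mg ATP (40 mcg/kg/min) twice daily was chosen in this study". That range is the only safety argument the article gives for the ATP dose.

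The same section gives the time limit and drip rate together: "IV administration should be completed within 40 min (40 drops per min) of time of dilution". The ATP (10 ml) is diluted in 100 ml of saline. The control volume matches that total: "patients will receive 110 ml of 0.9% saline in equivalent procedures".

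The Discussion explains that the 40 min limit belongs to PCr and is extended to the other arms for blinding, so that "both ATP and placebo group should be administered in less than 40 min". It then warns that "if the infusion rate of ATP is too fast, some patients might experience palpitations", and that nocebo effects may influence the efficacy results in the ATP group.

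The eligibility criteria set no weight limit, and no adjustment of the ATP dose or infusion time to weight is described. The only body weight in the article is in the PCr derivation: "IV administration of PCr at 1 g (125 mg/kg × 0.08 × 60 kg) twice daily was chosen in this study". No weight is given for ATP.

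**The concern.** The article treats a fixed dose (100 mg) and a per-kg rate (40 mcg/kg/min) as the same thing. They coincide at only one combination of weight and duration. The chosen figure is already the top of the cited range, so there is no room for lighter patients. The limit is a maximum duration, so by itself it sets a minimum rate and allows any faster one. As worded in the Interventions section it also runs from dilution, so a delay before the drip starts shortens the time left.

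Three things are at stake. First, safety is a main aim of the pilot, and the stated rationale does not cover patients below the threshold weight. Second, palpitations from fast ATP would occur in one arm and could reveal allocation, while blinding is itself a listed feasibility outcome. Third, the article already expects a nocebo influence on the ATP efficacy ratings, and variation in the delivered rate would make that harder to interpret.

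**Working it through.** **Inputs.** Dose 100 mg = 100,000 mcg, rate 40 mcg/kg/min, cited range 20–40 mcg/kg/min, limit 40 min, 40 drops/min and volume 10 + 100 = 110 ml (all Interventions); limit repeated as under 40 min (Discussion). The body weights below are illustrative, since the article gives no weight distribution. The drop factors are assumptions, since the article gives none.

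**1. Reproducing the stated 40 mcg/kg/min.**

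Rate = 100,000 / (minutes × kg).

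Over 40 min the flow is 100,000 / 40 = 2,500 mcg/min. The weight at which this is 40 mcg/kg/min is 2,500 / 40 = 62.5 kg. At 60 kg the rate is 2,500 / 60 = 41.7, about 4% above the stated figure. The stated figure is therefore a value for one weight of about 60 to 62.5 kg.

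**2. Rate by weight over a full 40 min.**

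| Weight (kg) | mcg/kg/min |
|---|---|
| 45 | 55.6 |
| 50 | 50.0 |
| 55 | 45.5 |
| 60 | 41.7 |
| 62.5 | 40.0 |
| 70 | 35.7 |

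**3. Threshold weight if the infusion is shorter.**

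Threshold = 100,000 / (minutes × 40).

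- 40 min: 62.5 kg
- 35 min: 71.4 kg
- 30 min: 83.3 kg

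Under the time limit, 62.5 kg is thus the most favourable threshold.

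**4. Drop rate against time limit.**

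40 drops/min × 40 min = 1,600 drops. For 110 ml this needs 1,600 / 110 = 14.5 drops/ml. For another factor f, duration = 110 × f / 40 min.

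| Assumed drops/ml | Duration (min) | Against the 40 min limit | Threshold weight (kg) | Rate at 60 kg (mcg/kg/min) |
|---|---|---|---|---|
| 10 | 27.5 | within | 90.9 | 60.6 |
| 15 | 41.25 | about 1 min over | 60.6 | 40.4 |
| 20 | 55 | 15 min over | 45.5 | 30.3 |

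A set that finishes well inside the limit widens the rate problem. A set that eases the rate problem breaks the limit. Dose, rate, 40 min and 40 drops/min all agree only at 62.5 kg with 14.5 drops/ml.

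**The case against.** The weight arithmetic is not in dispute, but several stronger readings are tempting and the article does not support them.

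- A reader might call 40 mcg/kg/min a safety ceiling. The article reports a range as safe. It names no maximum and does not say that higher rates are unsafe. The accurate statement is that lighter patients are above the upper end of the cited range.
- A reader might infer that the drop rate contradicts the time limit. Without a drop factor this is not established. The figures agree at 14.5 drops/ml, nearly agree at 15, and fit with time to spare at 10. A large misfit needs an assumed set of about 20 drops/ml, and under that assumption the threshold is 45.5 kg and no longer 62.5 kg. The two claims cannot both be made without conditions.
- A reader might say the speed has no upper bound. The stated 40 drops/min does fix the speed for a given set, so the 30 and 35 min cases show sensitivity only and are not protocol instructions. For the same reason, one should not join a 55 min infusion on an assumed set to a hypothetical 30 min infusion and present 30.3 to 55.6 mcg/kg/min at 60 kg as the spread the protocol allows.
- A reader might say many patients are affected. No weights are reported, so the number is unknown. The 60 kg figure belongs to the PCr derivation, and there the excess is only about 4%.

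It is also fair that the article handles part of the consequence. It admits the palpitation and nocebo risk, lists a blinding check, and includes palpitations in the side-effect scale. It schedules ECGs, keeps patients in hospital during the infusions, and treats efficacy as exploratory. The CRF is not shown, so one cannot say that weight or infusion times go unrecorded.

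All of this narrows the point. None of it makes a fixed dose equal to a fixed per-kg rate, and monitoring does not repair a rationale that rests on that equality.

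**Conclusion.** The figure is wrong as a general statement. With the 40 min limit governing, 100 mg matches the stated rate only at 62.5 kg, and every lighter patient receives more than the upper end of the range cited in support. The excess is small at 60 kg (41.7) and substantial at 50 kg (50.0) and 45 kg (55.6). This rests on the whole dose being infused over a full 40 min. Under that limit a shorter infusion can only raise the threshold. If the drip rate governed instead, the threshold would depend on an unstated drop factor: from 90.9 kg at 10 drops/ml to 45.5 kg at 20.

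The documents do not show that any delivered rate is unsafe, how many patients are affected, or that drip rate and time limit conflict. What they show is that the ATP safety rationale is stated for a rate the protocol does not deliver across the patients it can enrol.

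**What to change.** Reconcile the fixed dose, the per-kg rate, the time limit and the drop rate in the Interventions section and the Discussion, so that they describe one infusion. Which statement governs is for the clinical team; no value is proposed here. State the drop factor, so that drip rate and duration can be checked against each other. Then restate the safety rationale for the per-kg rates actually delivered over the enrolled weights.

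In the analysis, compute delivered mcg/kg/min for each ATP infusion from body weight and actual start and stop times, and report it beside adverse events and the blinding check. If the CRF does not already hold weight and the two times, add them.

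The cost is a change to the dosing text, which under the Protocol amendments section needs re-approval by the ethics committee and the sponsor, and a little more recording. The article says recruitment is ongoing. For patients already infused only the reporting part can apply, as far as their weights and times were recorded.

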### Discontinuation criteria

If participants meet one of the following criteria, the study drugs will be withdrawn:■ The drug-related utilization ratio (number of actual tablets taken/number of planned tablets × 100%) is less than 80% or greater than 120%■ The risks in continuing to participate outweigh the benefits of our study due to the appearance or exacerbation of other diseases■ The aggravation of patients’ mental conditions, such as evolution into severe depression or manic episodes, a high risk of suicide attempts or suicidal acts, which would require altering medical treatment during the study period■ Severe side effects, severe adverse events; and■ Anticipated or accidental pregnancy■ Patients can leave our trial at any time for any reason■ The reason for withdrawing should be recorded on the Case Report Form (CRF)

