### Combination therapies

■ We prefer that enrolled subjects with mild sleep difficulties not receive any sleeping pills. Zolpidem, zopiclone or estazolam will be prescribed for patients with severe insomnia disorders■ Enrolled subjects with other physical illnesses will continue with their original treatment plan■ Considering the precision of our collected clinical outcome data, antipsychotics, ADs or mood stabilizers (e.g., sodium valproate, lithium carbonate) will not be allowed to be prescribed during the study period. Similarly, any drugs that could have interactions with our study drugs, such as antiarrhythmic or antidiabetic drugs or tryptophan, will not be administered either■ The participants’ treatment history and concomitant treatments should be recorded on the CRF

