### Adherence

Before obtaining written informed consent, the patients will be comprehensively briefed on both the importance of conducting this clinical study and the value of their participation. Specifically, detailed information on our study procedure, its potential risks and its effectiveness will be conveyed to the subjects. Moreover, the economic burden of taking ADs can be partially alleviated, and subsidies, supported through funding, will be paid after they accomplish their follow-up assessments. During hospitalization, study drugs and doses will be monitored by the research nurse. Thus, medication compliance will be guaranteed. After discharge, the drug regimen and follow-up arrangement will be explained to the patients. The physician-patient relationship will be built on mutual respect and trust.

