**Table Taba:** 

Outcomes	
Recruitment period	
Feasibility outcomes	Our pilot study will be conducted in a general hospital. The difficulties while recruiting will be recorded and discussed in the final report. Regarding our study inclusion criteria, moderate to severe MDD patients with HAMD-24 ≥ 20 can be enrolled. Some of our eligible patients might be inclined to choose non-pharmacological treatment. The percentage of eligible patients refusing to participate in our study. Their reason will be recorded on the recruitment document and discussed in the final report. The percentage of eligible patients willing to participate in our study. Their reason will be recorded on the recruitment document and discussed in the final report
recruitment difficulties	
eligibility rate	
intention to use medication	
refusal rate	
participation rate	
Study period	
Feasibility outcomes	While hospitalized, the drug compliance will be guaranteed by bedside nurses. The assessment of adherence rate will follow schedule and their reason for not taking drugs will be recorded. (see Fig. 2). The percentage of enrolled patients withdrawn before completion of our study. Their reason will be recorded on the Case Report Form (CRF). If “yes,” the researcher should list the name/dosage/duration, and explain its reason for use on the CRF. After study period, the percentage of enrolled patients willing to receive medical advice from our clinical researcher. The occurrence rate of side effects or the adverse events. Test the conduction of our blinding method
adherence	
withdrawn	
concomitant therapy	
retention	
side effects/adverse events	
blinding	
Overall	
Feasibility outcomes	At any time of their participation, enrolled patients will be encouraged to report their suggestion or feeling to researcher. Also, they will receive a questionnaire questioning their perceptions toward the medical environment, treatment response, sense of security and suggestion while hospitalized. It will be recorded and discussed in final report. The appropriateness of the implementation of our study scheme and it will be discussed in final report
participation/hospitalization feedback	
study scheme	

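### Tablet use below 80% forces a drug stop in a pilot that counts adherence and withdrawal among its feasibility outcomes

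*Protocol article*

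**What the plan says.** The Discontinuation criteria section of the protocol article lists conditions, any one of which requires the study drugs to be stopped. The first is that "The drug-related utilization ratio (number of actual tablets taken/number of planned tablets × 100%) is less than 80% or greater than 120" per cent. The other conditions are risk outweighing benefit because of another disease, mental deterioration, severe side effects or adverse events, and pregnancy. The same list adds that "Patients can leave our trial at any time for any reason" and asks for the reason for withdrawal on the case report form.

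Under Interventions, fluoxetine is the only tablet, one a day, and "we will provide continuous orally administered fluoxetine therapy for 6 weeks". The infusions are confined to the 14-day hospital stay. Under Adherence, "During hospitalization, study drugs and doses will be monitored by the research nurse".

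The abstract names drug adherence, retention and drop-out as feasibility outcomes. The feasibility table says "The assessment of adherence rate will follow schedule and their reason for not taking drugs will be recorded", and also lists the percentage of enrolled patients withdrawn before completion.

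Under Combination therapies, "antipsychotics, ADs or mood stabilizers (e.g., sodium valproate, lithium carbonate) will not be allowed to be prescribed during the study period". Under Statistical analyses, primary results follow intention-to-treat, missing efficacy scores are filled by last observation carried forward (LOCF), and a sensitivity analysis uses the data without replacement.

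**The concern.** Research objectives gives the aim as feasibility and safety for a full-scale trial. How patients take fluoxetine once home, and how many withdraw, are among the things the pilot should find out. The lower limit acts on the quantity being measured: a patient who takes too few tablets is taken off the drug, and from then on that patient's own adherence cannot be seen. If the stop is also counted as a withdrawal, part of that percentage is made by the protocol and not by the patients.

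There is also a patient side. Harm, deterioration and pregnancy have their own criteria in the same list, so the 80% limit adds nothing for safety. It takes fluoxetine from someone with moderate to severe depression who may be taking nearly four tablets in five, during a period when other antidepressants are barred. The list foresees a change of treatment for patients who deteriorate ("which would require altering medical treatment during the study period"), but not for those who merely under-use. Nothing in the article softens the rule or gives a reason for it.

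**Working it through.** The article states no frequency for this rule, so there is no plan figure to reproduce. The check turns the limits into tablets and then shows how often and how late the rule would act under stated assumptions.

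**Inputs from the article**
- One tablet a day for 6 weeks: 6 × 7 = 42 planned tablets (Interventions).
- The first 14 are taken in hospital under supervision (Interventions, Adherence), leaving 42 − 14 = 28 outpatient tablets.
- 42 patients are randomized (Randomization and allocation concealment).
- The last assessment is at week 10, day 70 (Abstract).

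**Assumptions, not in the article**
- The ratio is taken over all 42 planned tablets. The article gives no counting window.
- All 14 inpatient tablets are taken.
- Outpatient days are independent, with the same daily probability p of taking the tablet; p = 0.90, 0.80 or 0.75.

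**Where the limits fall**
- Lower: 34/42 = 81.0% passes and 33/42 = 78.6% fails. Nine missed tablets trigger the stop, 9/28 = 32% of outpatient tablets.
- Upper: 50/42 = 119.0% passes and 51/42 = 121.4% fails.

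**How often the lower limit is crossed**

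The rule fires if at most 19 of the 28 outpatient tablets are taken: P(X ≤ 19), with X binomial (28, p).

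| p | P(rule fires) | × 42 patients |
|---|---|---|
| 0.90 | 0.0012 | 0.05 |
| 0.80 | 0.0900 | 3.8 |
| 0.75 | 0.2499 | 10.5 |

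**How late it acts**

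The outpatient day k of the ninth miss is negative binomial, conditional on k ≤ 28. Study day = 14 + k; dosing days left = 28 − k; days left to week 10 = 70 − (14 + k).

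| p | Mean k | Study day | Dosing days left | Days to week 10 |
|---|---|---|---|---|
| 0.90 | 25.5 | 39.5 | 2.5 | 30.5 |
| 0.80 | 24.6 | 38.6 | 3.4 | 31.4 |
| 0.75 | 24.0 | 38.0 | 4.0 | 32.0 |

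A patient who takes nothing after discharge has the ninth miss on day 14 + 9 = 23, with 42 − 23 = 19 dosing days and 70 − 23 = 47 days to week 10 left.

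**Sensitivity to the counting window**

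If the ratio were judged on each 14-day outpatient interval, 12/14 = 85.7% passes and 11/14 = 78.6% fails, so three misses suffice. P(X ≤ 11) with X binomial (14, p) is 0.16, 0.55 or 0.72 per interval for the same three values of p.

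On the 42-tablet base, then, little adherence is hidden for occasional missers. More is at stake if the window is shorter or if a stopped patient also leaves.

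**The case against.** The strongest reply is that the rule costs little information. On the 42-tablet base it fires only when the patient can no longer reach 80%, so that result is already known, and only about 2.5 to 4.0 dosing days are lost. Reasons for withdrawal are recorded, so forced and chosen exits can be separated afterwards. This stands, and it limits the size of the point. It does not explain why under-use should end treatment, and it depends on a counting window that the article does not give.

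Three stronger readings are tempting, and the documents support none of them.

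- **That the rule contradicts intention-to-treat.** It stops the drugs. Nothing says that the patient leaves the visits or the analysis. It changes the treatment received, not the set analysed.
- **That it distorts the efficacy results through LOCF.** This needs the stopped patient also to leave. The statement that patients may leave describes a right, not a consequence of the stop; subsidies are paid on completing follow-up assessments; and the unreplaced data are analysed too. The infusions, and the fast effect they are meant to show, fall in the supervised first 14 days, so the early comparisons are untouched. All arms take fluoxetine.
- **That it endangers the target of 12 patients per arm.** This needs drug stops to count as losses, and rates of under-use and of other drop-out that the article does not give.

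It is also fair that the full protocol may already say whether assessments continue after a drug stop. Silence in the article on that is not a fault.

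**Conclusion.** The point holds as a design matter. A mandatory stop for tablet use below 80% sits badly with a pilot that measures adherence and withdrawal, and it takes an antidepressant away without any sign of harm. The over-use limit is a different matter and has a plausible safety reason.

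The size cannot be computed from the article. On the 42-tablet base the share of patients affected runs from 0.1% to 25.0% as assumed daily intake falls from 0.90 to 0.75; interval counting would make it larger. The effect on group comparisons is probably modest. The percentage withdrawn is inflated only if drug stops are counted in it. The change is worth making because it is cheap and the rule has no stated purpose, not because it threatens the trial's conclusions.

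**What to change.** In the Discontinuation criteria, delete tablet use below 80% as a condition that requires the study drugs to be stopped. Say instead that under-use is recorded as an adherence result, with its reason, that treatment is still offered, and that scheduled assessments continue to week 10. Keep the stop for use above 120% and the existing safety stops. In the report, show drug stops required by the protocol separately from withdrawal from the study, using the reasons already collected.

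The cost is a change of wording and one line in a table, with no change to the sample size or the visit schedule. The downside is that a few poorly adherent patients stay on treatment, so adherence and group differences may look slightly less favourable.
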